## Abstract

According to World Health Organization (WHO) data, 16% of people are affected by infertility across the globe. One underlying factor is the age-related decline of ovarian reserve (DOR), which can lead to a higher chance of infertility and has no widely accepted treatment currently. Specific supplements and moderate exercise have been shown to improve fertility; however, there is no consensus to date on the type of exercise providing the best results. Our goal is to develop a novel exercise program combined with natural supplements for the improvement of fertility. We also propose a single-centered, randomized, open-label clinical trial using our newly developed exercise in the intervention group, compared to walking and no exercise in the other groups, to investigate the benefits of this exercise program in the future. In this study, we developed a structured, novel combination of exercises focusing on the pelvic and ovarian regions, core strengthening and improvement of blood circulation in this region. The 70 min full body “reproductive gymnastics”, includes strengthening, stretching, and relaxation exercises combined with yoga-inspired moves and diaphragmatic breathing with meditation elements to activate the parasympathetic pathway and stress relief. We believe we can improve fertility through the combination of natural supplements and our targeted, moderate physiotherapy program in women with DOR.

## 1. Introduction

Infertility is a growing concern worldwide, marked by the inability to achieve clinical pregnancy after a year of regular, unprotected intercourse [1]. Its global prevalence is significantly increasing, concurrently with the rising trend of delayed parenthood, and it affects an estimated 186 million people [2,3]. With increased maternal age, patients have to confront the decline in age-related ovarian reserve (DOR), which is well defined by the current determination of Anti-Müllerian Hormone (AMH), Antral Follicle Count (AFC), and basal FSH levels [4]. According to the American Society for Reproductive Medicine, the use of AMH and AFC as screening tests is most suitable for detecting poor ovarian response [5]. Since no single measure of ovarian reserve has 100% specificity in diagnosing DOR, a combination of biochemical and transvaginal ultrasound measurements (including FSH, LH, E2, AMH, and AFC) is utilized in this study to evaluate changes in ovarian reserve. Diminished ovarian reserve (DOR) is characterized by poor fertility indicators, even with the application of assisted reproductive techniques (ARTs), posing a significant challenge in reproductive medicine [6].

It has been shown that supplements have a high impact on the restoration of fertility. Myo-inositol has been demonstrated to improve ovarian function and increase the quality of oocytes, particularly in women with polycystic ovary syndrome (PCOS), leading to higher pregnancy rates [7,8]. In particular, several clinical trials demonstrate that its administration can have therapeutic effects in infertile women, and that it can also be useful as a preventive treatment during pregnancy [9].

Folic acid is essential for DNA synthesis and repair, and its supplementation is crucial for proper fetal development and reducing the risk of neural tube defects [10]. Melatonin not only regulates sleep but also acts as a potent antioxidant, protecting oocytes from oxidative damage and improving their quality [11,12,13]. Vitamins C and E, both powerful antioxidants, have been shown to reduce oxidative stress in the reproductive organs, thereby enhancing fertility, not only in woman [14,15]. Vitamin D3 plays a critical role in the modulation of the immune system and the regulation of reproductive processes, with deficiencies linked to adverse fertility outcomes [16]. Coenzyme Q10 is vital for mitochondrial function and energy production in oocytes, with studies indicating that its supplementation improves ovarian response and embryo quality [17,18]. Collectively, these supplements contribute to a comprehensive approach to restoring and enhancing fertility, addressing both physiological and biochemical factors involved in reproductive health.

The World Health Organization (WHO), and the American College of Obstetricians and Gynecologists (ACOG) suggests that women planning pregnancy should engage in at least 150 min of moderate physical activity per week, to reduce reproductive risks [19,20]. Not only does engaging in regular exercise improve fertility outcomes, but the specific type of physical activity plays a major role in enhancing reproductive health.

The coordinated, optimal functioning of the muscles involved in pelvic-lumbar (core) stabilization (diaphragm, pelvic floor muscles, transversus abdominis muscle (TVA), multifidus muscles) is of paramount importance for spinal protection, efficient breathing and movement, injury prevention, force transmission, optimal function and support of the pelvic floor and pelvic organs (ovaries, uterus), and proper regulation of sexual function. Pelvic-lumbar (core) stabilization is developed by strengthening the deep stabilization system of the spine, in coordination with the correct breathing pattern [21]. The proper muscle function of the TVA is of paramount importance for pelvic and lumbar stability, the restoration of physiological breathing patterns, and the efficient functioning of the pelvic floor muscles that work in co-contraction with it. Rehabilitation of the pelvic region and pelvic floor is essential to improving fertility. Exercises that improve pelvic-lumbar (core) stabilization have been shown to improve the function of the pelvic floor muscles, which play a crucial role in supporting the reproductive organs and improving blood supply to the ovaries and uterus [22]. Several authors agree that through breathing exercises, the complex trunk stabilization system can be directly affected [23,24,25]. Normal breathing mechanics play a key role in posture, optimal pelvic floor muscle function, and spinal stabilization.

Prolonged mental and physical stress, postural and lifestyle habits, and improper breathing patterns all contribute to diaphragmatic dysfunction. These factors also stimulate the sympathetic nervous system and stimulate the secretion of the stress hormone (cortisol), which also has a negative impact on fertility [26]. Additionally, diaphragmatic breathing has been shown to reduce stress, which is crucial for enhancing fertility, as chronic stress can disrupt hormone balance and menstrual cycles [27]. Yoga and diaphragmatic breathing, in particular, have demonstrated stress-reducing benefits, activating the parasympathetic nervous system and promoting a state of relaxation conducive to reproductive health [28,29].

These professional aspects should be combined in a targeted and comprehensive multidimensional exercise program.

Despite these promising findings, further research is needed to confirm these effects due to the limited number and sample size of previous studies and the current ambiguity in exercise recommendations for improving fertility outcomes.

In this study, we present a novel and innovative therapeutic exercise protocol specifically designed for pelvic region rehabilitation and ovarian rejuvenation. The therapeutic exercises focus on improving fertility, rehabilitation of the pelvic region (including re-education of the pelvic floor muscles), teaching correct posture, improving the pelvic-lumbar core stabilization system, restoring optimal muscular function of the diaphragm, and activating the parasympathetic nervous system through learning stress-relieving breathing and relaxation. These exercises are expected to enhance pelvic circulation and improve muscle function, which are crucial for reproductive health, especially in patients with diminished ovarian reserve (DOR).

The primary objective of this study is to assess the ovarian rejuvenating effect of this specific exercise program before IVF/ICSI cycles or spontaneous pregnancy, confirming the reproductive efficacy of this regimen. We also aim to improve stimulation and oocyte quality in patients who meet the inclusion criteria, partly by improving pelvic and ovarian circulation (ovarian rejuvenation exercise, the subject of this study) and partly by enhancing cumulus corona radiata and granulosa cell function (per os rejuvenation therapy).

It is expected that our results will show that AMH will be increased, basal FSH levels will be decreased, cycle length will be optimized (getting closer to 28–30 days), fertility rates and stimulation will be improved, and spontaneous pregnancy will be detected at the end of the process. If this investigation confirms the efficacy of the specific exercise program in DOR patients, this could make a useful contribution to fertility treatment in this poorly manageable patient population.

## 2. Experimental Design

This protocol was written in accordance with the Standard Protocol Items: Recommendations for Interventional Trials (SPIRIT) reporting template [30]. This was a single-center, randomized (1:1:1), open-label clinical trial, with three treatment groups: per os therapy (Group A), per os therapy and walking (Group B), per os therapy and special exercise (Group C). The purpose of randomization is to eliminate selection bias. The study protocol was approved and registered by the Human Reproduction Committee of Hungarian Medical Research Council (25489-8/2021/EÜIG).

### 2.1. Study Setting

This study will involve women aged 20–42 diagnosed with diminished ovarian reserve (DOR) who meet the following criteria: (1) AMH levels < 1.1 ng/mL at the beginning of the cycle, (2) BMI between 18.5 and 30 kg/m^2^, (3) regular and normal menstruation, and (4) specified hormone levels (TSH < 2.5 mIU/mL, vitamin D3 > 75 nmol/L, Prolactin < 24 ng/mL). We plan to enroll 120 patients between January 2025 and December 2025.

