### 2.2. Eligibility Criteria

#### 2.2.1. Inclusion Criteria

Participants who meet the following inclusion criteria will be included: (1) female of reproductive age 20–42 years; (2) BMI: 18.5–30 kg/m^2^; (3) regular menstruation; (4) anti-Müllerian hormone (AMH) <  1.1 ng/mL; (5) hormone levels: TSH < 2.5 mIU/mL, vitamin D3: >75 nmol/L, Prolactin: <24 ng/mL; (6) understanding the study design, risks, and benefits, and providing informed consent; and (7) the ability to comply with the study protocol.

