#### 2.3.1. Primary Outcome

The primary outcome is the change in FSH and AMH levels compared with the levels before. Spontaneous pregnancy during the study period will be recorded as a primary outcome measure.

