### 2.5. Statistical Methods

Descriptively, we intend to calculate the mean, standard deviation, minimum, maximum, and range of data, while the occurrence of spontaneous pregnancy will be presented as a percentage. For the evaluation of results, after conducting the Shapiro–Wilk normality test, paired T-tests or Wilcoxon tests will be used to compare baseline and three-month laboratory results within each group, and one-way analysis of variance (ANOVA) or Kruskal–Wallis’s test, along with Tukey’s post hoc test, will be used for comparison among the three groups. Chi-square tests or Fisher’s exact tests are planned to be applied for comparing the numbers or percentages between groups.

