### 2.7. Implementation

The principal investigator or a designated sub-investigator will input the required data into a web-based allocation system for eligible patients. Subsequently, the system will allocate participants to the three investigated groups. The required data include personal data, demographic data, medical and family history, body composition assessment (weight, height, BMI), menstrual cycle (length and days of menstruation), hormone levels (AMH, FSH, LH, E2, PRL, TSH, vitamin 25-OH-D3), progesterone levels, and the FSFI questionnaire, as shown in Table 1.

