### 4.6. Baseline Assessments

Baseline assessments will adhere to the trial’s standard operating procedure (SOP). During the first visit, between days 2 and 4 of the cycle, a laboratory examination will be conducted, including hormone levels of AMH, FSH, LH, E2, PRL, TSH, 25-OH-D3 vitamin, and progesterone. Baseline progesterone will be measured between days 21 and 22 of the same cycle. The FSFI questionnaire will also commence during this phase.

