## Figures and Tables

**Figure 1 life-15-00018-f001:**
[figure not shown]
Trial design.

**Table 1 life-15-00018-t001:** Study Assessments and Procedures.

	Screening	Baseline (2–4. Day of Menstrual Cycle)	Baseline (21–22. Day of the Same Cycle)	3 Months (2–4. Day of Cycle)	3 Months (21–22. Day of the Same Cycle)
Assessment					
Investigator meetings	✓				
Informed consent	✓				
Demographics, medical, and family history	✓				
Body composition assessment (Weigh, Height, BMI)	✓			✓	
Menstrual cycle	✓			✓	
Hormone levels (AMH, FSH, LH, E2, PRL, TSH, 25-OH-D3 vitamin)		✓		✓	
Progesteron		✓	✓		✓
FSFI questionnaire		✓		✓	
Spontaneous pregnancy				✓	

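### If the day 2–4 AMH sample both qualifies a woman and serves as her baseline, regression to the mean pushes the within-arm AMH tests towards a rise in all three arms; the between-arm comparison is not biased

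*Protocol article*

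**What the plan says.** - **Entry.** Section 2.1 requires "AMH levels < 1.1 ng/mL at the beginning of the cycle". Section 2.2.1 repeats the cut-off without saying when the sample is taken or whether it may be an earlier one.
- **Baseline.** Section 4.6 states: "During the first visit, between days 2 and 4 of the cycle, a laboratory examination will be conducted, including hormone levels of AMH".
- **Schedule.** The Table 1 row beginning "Hormone levels (AMH, FSH, LH, E2, PRL, TSH, 25-OH-D3 vitamin" is ticked at baseline (day 2–4) and at three months (day 2–4). Its Screening cell is empty.
- **Allocation.** Under section 2.7 the investigator "will input the required data into a web-based allocation system for eligible patients", and AMH is among those data.
- **Outcome.** Section 2.3.1: "The primary outcome is the change in FSH and AMH levels compared with the levels before".
- **Analysis.** Section 2.5: "paired T-tests or Wilcoxon tests will be used to compare baseline and three-month laboratory results within each group". ANOVA or Kruskal–Wallis with Tukey's test "will be used for comparison among the three groups". Section 2.3.2 places the comparison of the three groups among the secondary outcomes.
- **Expectation.** The Introduction expects AMH to go up.

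**The concern.** Selecting on a noisy measurement below a cut-off brings in some women whose true level is at or above the cut-off but whose reading happened to be low. It also keeps out women whose true level is below it but whose reading was high. If that same reading is the baseline, the baseline mean is too low and a repeat measurement is higher on average, with no treatment effect.

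AMH change is a primary outcome, is worded as before against after, and is to be tested by paired tests in each arm. An apparent rise would look like the hoped-for ovarian rejuvenation. This matters most for Arm A: it takes supplements only, the trial has no untreated group, and randomisation therefore cannot expose a false rise attributed to the supplements. The AMH change quoted for Arm C on its own would be inflated in the same way.

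**Working it through.** **1. The plan's own figure.** For a three-group ANOVA with f = 0.4, alpha 0.05 and power 0.95, the noncentrality is f² × N = 0.16 × 102 = 16.32. The power at N = 102 is 0.955, and 102 is the smallest balanced total reaching 0.95. Then 34 / (1 − 0.15) = 40 per group, 120 in all. Section 2.4 reproduces and is not affected by this point. The check below uses its 34 per arm.

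**2. Inputs.** From the documents: the cut-off c = 1.1 ng/mL, one pre-treatment AMH, one at three months, and 34 per arm. Assumed, because the documents give none of them: log-normal true AMH with source median m and between-woman log-SD s; independent within-woman variation (biology plus assay) with log-SD w, where w² = ln(1 + CV²); no treatment effect and no time trend.

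**3. Expected shift when one sample serves both purposes.** Let σ² = s² + w² and z = (ln c − ln m)/σ. The mean log change is (w²/σ) × φ(z)/Φ(z).

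- Middle case, m = 1.1, s = 0.5, CV 20%: w² = ln 1.04 = 0.0392, σ = √0.2892 = 0.538, z = 0, φ/Φ = 0.3989/0.5 = 0.798. Shift = 0.0392/0.538 × 0.798 = 0.058, a rise of 6.0% in the geometric mean.
- Mildest case, m = 0.8, s = 0.8, CV 10%: w² = 0.00995, σ = 0.806, z = 0.395, φ/Φ = 0.565. Shift = 0.0070, or 0.7%.
- Most severe case, m = 2.0, s = 0.5, CV 30%: w² = 0.0862, σ = 0.580, z = −1.031, φ/Φ = 1.55. Shift = 0.230, or 26%.

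**4. Simulation (2,000,000 women per scenario, then arms of 34, paired t-test at two-sided 0.05).**

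| Assumptions | Rise, geometric mean | Rise, arithmetic mean | Significant rise, log scale | Significant rise, raw scale |
|---|---|---|---|---|
| m 0.8, s 0.8, CV 10% | 0.7% | 1.3% | 5% | 6% |
| m 0.8, s 0.6, w 0.15 | 1.8% | 3% | 7% | 10% |
| m 1.1, s 0.5, CV 20% | 6.0% | 8.7% | 22% | 34% |
| m 1.2, s 0.6, w 0.30 | 12.6% | 19% | 37% | 58% |
| m 2.0, s 0.5, CV 30% | 26% | 34% | 91% | 98% |

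The last two columns count significant rises only, so the nominal rate is 2.5%. Over a grid of 24 scenarios (m 0.8–2.0, s 0.5 or 0.8, CV 10–30%) the shift was positive every time, from 0.008 to 0.284 ng/mL. In the middle case, the chance that at least one of three arms is significant on the raw scale is 1 − (1 − 0.341)³ = 0.71.

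**5. Between-arm comparison.** In the same 24 scenarios, ANOVA of change across three arms rejected in about 4–6%, against 5% nominal. The shift is equal in expectation in all arms and cancels.

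**6. Separate qualifying sample.** With eligibility decided on a different reading, the mean null change was about 0.000 ng/mL and the paired test rejected in 4.7–4.8% (two-sided) in the three scenarios run. The share of admitted women whose baseline then exceeds 1.1 ng/mL is arccos(ρ)/π in the middle case. There ρ = 0.25/0.2892 = 0.864, which gives 0.527/3.142 = 17%.

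**The case against.** **The shared sample is inferred.** A reader might take it as a stated fact that one sample does both jobs. No section says so. Table 1 is not a full list of eligibility tests: the antral follicle count is an exclusion criterion in section 2.2.2, yet it has no row there. Section 2.1 enrols women already diagnosed with DOR, so an earlier AMH may exist, and section 4.6 refers to an operating procedure that is not shown. This stands, and the point is therefore conditional. It does not remove the point: no section makes an earlier value the qualifying one, and the only scheduled draw matches the timing in section 2.1.

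**The randomised comparison is sound.** A reader might infer that the trial's comparison of exercise with control is biased. It is not, as step 5 shows. Section 2.3 frames the objective as a comparison with the other groups, and section 2.4 sizes the trial on one. What remains is confined to the paired tests and per-arm changes, which could not isolate a treatment effect even with a clean baseline. They matter here because section 2.3.1 words the primary outcome as before against after and section 2.3.2 makes the group comparison secondary.

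**The size is uncertain.** At the mild end the artefact is negligible, and a true AMH decline over three months would offset part of it. A rise in every arm is an expectation, not a prediction for each arm. This also stands.

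**Other hormones.** The entry limits on TSH, prolactin and vitamin D act in the same way, but none of these is a listed primary or secondary outcome. FSH, the other hormone in the primary outcome, has no entry limit and is not directly affected.

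**Conclusion.** The concern holds as a conditional, limited point. If the day 2–4 sample decides eligibility, as the schedule suggests, the within-arm AMH tests and per-arm AMH changes are biased towards a rise in all three arms. The direction follows from the design. The size does not: it rests wholly on the assumed source median and variances. Under those assumptions the rise runs from about 1% to 13% or more, with false significant rises in about 5% to over 50% of arms against 2.5% nominal. The documents support no claim of bias in the between-arm comparison or in the sample size. It is worth correcting before analysis, because the artefact points the same way as the hoped-for result and the correction is nearly free.

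**What to change.** 1. In section 2.5, state that within-arm AMH change is descriptive only and includes regression to the mean. Base the AMH efficacy conclusion on the comparison between the three arms, adjusted for baseline AMH (for example by ANCOVA). This is enough by itself to prevent a false efficacy claim, whichever sample decides eligibility.
2. Where an AMH result from the start of a cycle is already on file from the DOR diagnosis, state in section 2.2.1 and in the Screening column of Table 1 that this result decides eligibility. The day 2–4 sample is then the baseline whatever its value. This depends on such results existing and being comparable in assay and cycle timing, which the documents do not establish. Where none exists, item 1 covers the case.

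**Cost.** Wording only; no extra draw, and no change to randomisation or sample size. Within-arm p-values lose confirmatory status. Under item 2, some women will have a baseline AMH above 1.1 ng/mL, mostly by a small margin. The 17% in step 6 is an illustration under the middle assumptions, and the share falls if within-woman variation is smaller.

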### 2.2. Eligibility Criteria

#### 2.2.1. Inclusion Criteria

Participants who meet the following inclusion criteria will be included: (1) female of reproductive age 20–42 years; (2) BMI: 18.5–30 kg/m^2^; (3) regular menstruation; (4) anti-Müllerian hormone (AMH) <  1.1 ng/mL; (5) hormone levels: TSH < 2.5 mIU/mL, vitamin D3: >75 nmol/L, Prolactin: <24 ng/mL; (6) understanding the study design, risks, and benefits, and providing informed consent; and (7) the ability to comply with the study protocol.

#### 2.2.2. Exclusion Criteria

Participants meeting any of the following criteria will be excluded: (1) age > 42 years old; (2) antral follicle count (AFC) <  3 measured on day 2 of the cycle; (3) multiple unsuccessful stimulation cycles ending with cancellation; (4) allergy to medications used for ovarian rejuvenation; (5) three or more ovarian surgeries result in significant ovarian reserve depletion (iatrogenic POI, iatrogenic DOR); (6) secondary amenorrhea; (7) uterine developmental abnormalities; and (8) inability to engage in physical activity.

### 2.3. Objectives

The primary objective of this study is to assess the efficacy of specific exercise routine on ovarian function compared with a standard of care and low intensity walking in patients with diminished ovarian reserve, by optimizing hormone levels for better stimulation possibilities.

#### 2.3.1. Primary Outcome

The primary outcome is the change in FSH and AMH levels compared with the levels before. Spontaneous pregnancy during the study period will be recorded as a primary outcome measure.

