#### 2.3.2. Secondary Outcomes

The secondary outcomes include: optimization of E2 and LH levels; optimization of menstrual cycle length; change in BMI level; improvement in quality of life using the FSFI questionnaire; and comparing the effectiveness between the 3 study groups.

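### The randomised between-arm comparison is ranked as a secondary outcome and the primary outcome is worded as a before-after change, against the comparative objective and the three-group sample size

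*Protocol article*

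**What the plan says.** All references are to the protocol article.

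- **2.3 Objectives.** The primary objective is comparative: to "assess the efficacy of specific exercise routine on ovarian function compared with a standard of care and low intensity walking".
- **2.3.1 Primary Outcome.** "The primary outcome is the change in FSH and AMH levels compared with the levels before". The only comparator named is the woman's own earlier value. Pregnancy is added: "Spontaneous pregnancy during the study period will be recorded as a primary outcome measure".
- **2.3.2 Secondary Outcomes.** The last item is "comparing the effectiveness between the 3 study groups".
- **2.4 Sample Size.** The total of 102, raised to 120, comes from a one-way ANOVA with three groups, effect size 0.4, alpha 0.05 and power 0.95.
- **2.5 Statistical Methods.** "paired T-tests or Wilcoxon tests will be used to compare baseline and three-month laboratory results within each group". The same sentence adds ANOVA or Kruskal-Wallis with Tukey's post hoc test, which "will be used for comparison among the three groups". Chi-square or Fisher tests compare percentages between groups. No analysis is named as primary.
- **4.1 Intervention.** All three arms take the same oral supplements; Arm B adds walking and Arm C adds the exercise programme.
- **4.7 Efficacy Assessments.** The change in FSH and AMH is again called primary, with no contrast between arms.

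**The concern.** The objective and the sample size rest on the difference between arms. The outcome sections place that difference below the change from baseline. This is more than a detail left to an analysis plan: 2.3.2 gives the comparison a rank, and an analysis plan that made it primary would contradict that section.

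The ranking matters because a before-after change in Arm C has several possible sources. The supplements are given as active therapy in every arm. Three months pass. Entry also requires "AMH levels < 1.1 ng/mL at the beginning of the cycle", so AMH may rise on re-measurement through regression to the mean, which is the direction the Introduction predicts as benefit. Only the comparison with Arms A and B removes these shared influences. If a paired result in Arm C were reported as the primary finding, it could be credited to exercise when exercise had contributed nothing. A significant result in C beside a non-significant one in A or B would not repair this, since it is not a test of the difference.

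**Working it through.** **1. The plan's own figure.** Inputs from 2.4: k = 3 groups, effect size f = 0.4, alpha = 0.05, power 0.95. For the omnibus F test the noncentrality is N × f², with 2 and N − 3 degrees of freedom.

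- N = 99: 99 × 0.16 = 15.84, power 0.949.
- N = 102: 102 × 0.16 = 16.32, power 0.955.
- N = 120: 120 × 0.16 = 19.2, power 0.979.

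The smallest multiple of 3 that reaches 0.95 is 102, as stated. Dropout: 102 / 0.85 = 120 and 34 / 0.85 = 40. The arithmetic is correct, and it is the arithmetic of a between-arm test.

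**2. Paired test in Arm C when exercise adds nothing.** Suppose all three arms change by the same standardised amount dz (mean change divided by the SD of change). The document gives neither an SD nor an expected change, so dz is an assumption. With n = 34, the paired t statistic has 33 degrees of freedom and noncentrality dz × √34 = 5.83 × dz. The test is two-sided at 0.05, counting only the favourable direction.

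| dz (assumed) | Noncentrality | Arm C significant | Arm C significant, ANOVA not |
|---|---|---|---|
| 0 | 0 | 2.5% | not run |
| 0.2 | 1.17 | 20% | 19% |
| 0.3 | 1.75 | 40% | 38% |
| 0.5 | 2.92 | 81% | 78% |

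The between-arm ANOVA on the change rejects in about 5% of these trials at each of the three non-zero values. The last column is from simulation. In the same simulations, Arm C is significant while at least one control arm is not in about 34% of trials at dz = 0.3 and 28% at dz = 0.5, although the true changes are identical.

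**3. Regression to the mean in AMH.** This applies only if the value that qualifies a woman is also her baseline value. Table 1 shows no hormone draw at screening, and 4.6 places the draw at the first visit, which suggests one draw but does not say so. Assumptions: log-normal AMH, between-woman log SD 0.8, no true change, 34 per arm, entry below 1.1 ng/mL. The entries are the chance of a falsely significant rise in a given arm, against a nominal 2.5% in that direction.

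| Source median (ng/mL) | Within-woman log SD 0.1 | 0.2 | 0.3 |
|---|---|---|---|
| 2.0 | about 10% | about 25% | about 46% |
| 1.0 | 5.5% | 11% | 18% |

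At a source median of 0.7 the range is 4–10%. If baseline is a separate draw taken after qualification, the rate returns to 2.5% in every case. In all these scenarios the between-arm ANOVA on change rejects in about 5%.

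**4. What ranking the comparison first does to power.** The objective names two comparators. Under Tukey, power to show C better than both A and B depends on how f = 0.4 is spread over the arms, which 2.4 does not give.

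- A = B < C: difference 0.4 × 3 / √2 = 0.85 SD. Power for both contrasts is 0.78 at 34 per arm and 0.86 at 40.
- Equally spaced means: C − A = 0.4 × 2 / √(2/3) = 0.98 SD, C − B half of that. Power for both is 0.36 at 34 per arm and 0.43 at 40.

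**The case against.** The strongest reply is that 2.3.1 only defines a variable. A change score is an ordinary endpoint in a randomised trial, 2.3.1 names no test, and 2.5 does plan the between-arm ANOVA or Kruskal-Wallis with Tukey. Read with 2.3 and 2.4, the authors probably intend that comparison to carry the conclusion. Much of this stands. A reader of 2.3.1 might infer that the plan has no randomised test of the primary outcome, or that the trial has a rule by which it may claim success on Arm C alone. The document supports neither: the test is planned, and no success criterion is stated anywhere. What the reply does not remove is the explicit secondary ranking in 2.3.2 and the silence in 2.5 on which test is primary.

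A second reply concerns regression to the mean. Participants already carry a diagnosis of diminished reserve and come from an assisted reproduction centre (2.1, 2.6), so an earlier clinical AMH could be the qualifying value. That stands too, and it makes the figures in step 3 conditional. They also depend on SDs and a source median that are not in the document, and they concern AMH only, since FSH is not an entry criterion. The main argument needs none of them: the supplements shared by all arms are enough.

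**Conclusion.** The point holds as an internal contradiction about rank. Sections 2.3.1 and 2.3.2 place the before-after change above the randomised comparison, against the primary objective in 2.3 and the sample size in 2.4. Since 2.5 does not settle the matter, the text permits a before-after result in Arm C to be presented as the primary finding. It does not require that, and it does not omit the between-arm test.

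On size: with a shared standardised change of 0.3 to 0.5 and no exercise effect, a paired test in Arm C is significant in about 40% to 81% of trials, against about 5% for the between-arm ANOVA. These figures rest on the assumed dz and 34 evaluable women per arm. Regression to the mean may add to this for AMH, at roughly 5–46% per arm for source medians of 1.0 to 2.0, but only if one draw serves as both qualifying and baseline value. Because the ranking determines what the trial's primary claim is, it should be corrected before any results are analysed.

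**What to change.** - **2.3.1:** keep the existing primary outcomes and state that their primary analysis is the between-arm comparison. For FSH and AMH, compare the 3-month level adjusted for the baseline value, using the three-group test for which 2.4 sizes the trial, followed by the planned Tukey-type contrasts C vs A and C vs B. For spontaneous pregnancy, use the between-group chi-square or Fisher test already in 2.5.
- **2.3.2:** delete "comparing the effectiveness between the 3 study groups".
- **2.5:** make the paired within-arm tests descriptive: mean change with confidence interval and no conclusion about efficacy.
- **2.4:** state that the 0.95 power applies to the omnibus test only, and give the power for C against both A and B under a named pattern of means (about 0.78 at 34 per arm if A = B < C, about 0.36 if equally spaced).
- **Table 1 or 4.6:** say whether the AMH value that qualifies a woman is also her baseline value.

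The cost is wording. No further visit or measurement is needed, because baseline and 3-month values are already collected. No extra patients are needed for the omnibus test. The downside is that the claim the objective implies, exercise better than both comparators, has less power than the stated 0.95. The present plan has that limit too, but does not show it.
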